## Abstract

**Background:**

*Klebsiella pneumoniae* liver abscess is the most common etiology of liver abscess in Singapore and much of Asia, and its incidence is increasing. Current management includes prolonged intravenous antibiotic therapy, but there is limited evidence to guide oral conversion. The implicated K1/K2 capsule strain of *Klebsiella pneumoniae* is almost universally susceptible to ciprofloxacin, an antibiotic with high oral bioavailability. Our primary aim is to compare the efficacy of early (< one week) step-down to oral antibiotics, to continuing four weeks of intravenous antibiotics, in patients with Klebsiella liver abscess.

**Methods/design:**

The study is designed as a multi-center randomized open-label active comparator-controlled non-inferiority trial, with a non-inferiority margin of 12%. Eligible participants will be inpatients over the age of 21 with a CT or ultrasound scan suggestive of a liver abscess, and *Klebsiella pneumoniae* isolated from abscess fluid or blood. Randomization into intervention or active control arms will be performed with a 1:1 allocation ratio. Participants randomized to active control will receive IV ceftriaxone 2 grams daily to complete a total of four weeks of IV antibiotics. Participants randomized to intervention will be immediately converted to oral ciprofloxacin 750 mg twice daily. At Week four, all participants will undergo abdominal imaging and be assessed for clinical response (CRP < 20 mg/l, absence of fever, plus scan showing that the maximal diameter of the abscess has reduced). If criteria are met, antibiotics are stopped; if not, oral antibiotics are continued, with reassessment for clinical response fortnightly. If criteria for clinical response are met by Week 12, the primary endpoint of clinical cure is met. A cost analysis will be performed to assess the cost saving of early conversion to oral antibiotics, and a quality of life analysis will be performed to assess whether treatment with oral antibiotics is less burdensome than prolonged IV antibiotics.

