### Objectives

The primary objective is to compare the rate of clinical cure after four weeks of IV antibiotics to early step-down to oral antibiotics in patients with *Klebsiella pneumoniae* liver abscess, with clinical cure determined at Week 12 post randomization, and defined as CRP < 20 mg/l, plus absence of documented fever ≥ 38°C in the preceding seven days, plus most recent abdominal imaging showing that the maximal diameter of the abscess has reduced. The main secondary objective is to compare the rate of clinical response between the two study arms, with clinical response determined at Week 4 post-randomization, and defined as per clinical cure. Other secondary objectives are to compare the rate of the following during the study period, between the two study arms (assessed at 12 weeks): all cause mortality; unplanned readmission for any cause; unplanned need for drainage; metastatic complications; recrudescent or breakthrough *K. pneumoniae* bacteremia; need to escalate antibiotics due to worsening infection or secondary infection; vascular catheter complications. Additionally, to compare the length of hospital stay (from the date of randomization to the end of inpatient stay), length of time the subject requires medical leave following hospital discharge (censored at 12 weeks), total cost, subject quality of life (QoL), and adherence to study drug between the two study arms.

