Following discharge, participants in both arms of the study will be reviewed weekly in the OPAT clinic with a standardized clinical assessment consisting of temperature, blood pressure, heart rate, symptom assessment, clinical examination and blood tests (FBC, RP1, LFT, CRP, procalcitonin) as well as an adherence check for both study arms (pill count for subjects on oral; OPAT nurse documentation and infusion bottle count for subjects on IV). Within the three days preceding the Week 4 visit, all study participants will undergo follow-up abdominal imaging (CT or US) as per current standard of care in these cases. If participants do not meet criteria for clinical response at Week 4, there will be a further Week 6 appointment at the end of the two week extension of oral antibiotics. Patients not satisfying the criteria for clinical response after Week 6 will receive two weekly extensions of oral antibiotics and two weekly visits, until they meet criteria for response. Patients not meeting criteria for clinical response by the Week 6 visit will have a repeat abdominal scan (CT or US) arranged for within three days prior to the Week 8 visit. Patients not meeting criteria for clinical response by the Week 10 visit will have a repeat abdominal scan (CT or US) arranged for within three days prior to the Week 12 visit. There is no upper limit to the duration of antibiotics, but subjects will not be followed up beyond Week 12 within the study. Patients not meeting criteria for clinical response by the Week 12 visit will have failed to meet the primary endpoint of clinical cure, and will thereafter revert to routine clinical care.

All participants will return to a follow-up assessment at Week 12. This assessment will follow the same format as the preceding visits, with standardized clinical assessment consisting of temperature, blood pressure, heart rate, symptom assessment, clinical examination and blood tests (FBC, CRP, and procalcitonin).

The following direct and indirect costs over the whole study period will be collected from administrative sources where possible, and by self-report otherwise. Patients will be asked to maintain a diary of health care-related utilization and expenditures as well as to retain all related receipts and bills collected during the period of the study.

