### Study endpoints

The primary endpoint is 'clinical cure’, determined at Week 12 post-randomization, and defined as CRP < 20 mg/l, plus absence of documented fever ≥ 38°C in the preceding week, plus most recent abdominal imaging showing that the maximal diameter of the abscess has reduced.

The main secondary endpoint is 'clinical response’, determined at Week 4 post-randomization, and defined as CRP < 20 mg/l, plus absence of documented fever ≥ 38°C in the preceding week, plus most recent abdominal imaging showing that the maximal diameter of the abscess has reduced. Other secondary endpoints (assessed at Week 12) are:

• all-cause mortality at any point between randomization and Week 12;

• unplanned readmission for any cause at any point between hospital discharge and Week 12;

• unplanned need for drainage after enrollment at any point between randomization and Week 12 (the screening visit will document any plans for elective drainage);

• metastatic complications occurring at any point between randomization and Week 12;

• new *K. pneumoniae* bacteremia occurring at any point between the first negative blood culture, and Week 12, with the same strain of *K. pneumoniae* as the original blood culture or abscess fluid culture determined by antibiotic susceptibility pattern);

• length of hospital stay (from the date of randomization to the end of inpatient stay, censored at Week 12);

• length of time the subject requires medical leave following hospital discharge (censored at Week 12);

• subject quality of life as defined by the WHOQOL-BREF assessed at Week 4 and Week 12 post-randomization;

• overall cost of each treatment strategy from the payer and total societal perspective for the course of the study until the final 12 Week follow-up;

• level of adherence during the entire study period, assessed at 12 weeks. Subject deemed to be compliant if 80% or more of prescribed antibiotics have been taken.

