Safety endpoints include: need to stop study drug due to toxicity; toxicity as defined by Common Terminology Criteria for Adverse Events version 4.03 [17]; all adverse events (occurrence of adverse events up to 12 weeks post randomization or 30 days post last study dose if later than 12 week visit); serious adverse events (occurrence of serious adverse events at any time during the study period, whether or not they are thought to be related to the study drugs); need to escalate antibiotics due to worsening infection or secondary infection at any point between randomization and Week 12; vascular catheter complications at any point between randomization and Week 12.

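### The abstract scores primary cure as criteria met by Week 12, the Objectives and Study endpoints as status at Week 12; align them, and add a supportive analysis because rescued patients can count as cured

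*Protocol article*

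**What the plan says.** The protocol article describes the primary endpoint in four places.

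- **Abstract, Methods/design:** "If criteria for clinical response are met by Week 12, the primary endpoint of clinical cure is met".
- **Objectives:** the comparison is of cure rates, "with clinical cure determined at Week 12 post randomization".
- **Study endpoints:** cure is "determined at Week 12 post-randomization, and defined as CRP < 20 mg/l, plus absence of documented fever ≥ 38°C in the preceding week", together with a smaller maximal abscess diameter on the latest scan.
- **Study visits and procedures:** "Patients not meeting criteria for clinical response by the Week 12 visit will have failed to meet the primary endpoint of clinical cure".

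The events that would mark a clinical setback are listed separately. Secondary endpoints include "unplanned need for drainage after enrollment at any point between randomization and Week 12", metastatic complications and new bacteremia with the same strain. A safety endpoint is "need to escalate antibiotics due to worsening infection or secondary infection at any point between randomization and Week 12". None of them makes a patient a primary failure. Non-responders in both arms receive repeated two-week oral extensions, and "There is no upper limit to the duration of antibiotics".

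**The concern.** The non-inferiority claim rests on this one endpoint, so a patient's score must not depend on which section is read. Under the abstract's rule a patient who has once met the criteria has already reached the endpoint, and nothing later can undo it. Under the Objectives and Study endpoints, what counts is the patient's state at Week 12.

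The second part applies under both readings. The definition has three components (CRP, fever, diameter) and is silent on what it took to get there. A patient who worsened, was drained or escalated, and then looked well at Week 12 is a cure. So is a patient who first meets the criteria at the Week 12 visit after taking antibiotics up to that day. If such patients are more frequent in the oral arm, the observed difference is smaller than the difference in how well the allocated treatment worked, and that favours a finding of non-inferiority.

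**Working it through.** **1. The readings side by side**

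| Patient | Abstract (by Week 12) | Objectives, Study endpoints (at Week 12) |
|---|---|---|
| Responds at Week 4, well at Week 12 | cure | cure |
| Responds at Week 4, fever or CRP ≥ 20 mg/l at Week 12 | cure | failure |
| Responds at Week 4, dies before Week 12 | cure | not a cure, but not expressly a failure |
| Never meets criteria by Week 12 | failure | failure |

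The sentence in Study visits and procedures covers only the last row, so it fits either reading. In the second row it is CRP and fever that can change. Under the Table 1 footnotes the Day 84 scan is done only in patients who still fail at Day 70, so an early responder's imaging component normally comes from the Week 4 scan.

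Death needs its own sentence. The Statistical analysis section defines the per-protocol set as patients with the primary endpoint measured. Without a stated rule, a death could be left out of that set rather than scored.

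**2. The plan's own figure**

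Inputs from Determination of sample size: 95% cure in the control arm (taken as equal in both arms), margin 0.12, one-sided 0.025, power 0.80. Exact enumeration of the unpooled z-test with continuity correction, z = (p_T − p_C + 0.12 − 1/n) / √[p_C(1−p_C)/n + p_T(1−p_T)/n], gives power 0.753 at n = 63 and 0.807 at n = 64. With 15% attrition, 64/0.85 = 75.3, so 76 per arm and 152 in total. The stated size reproduces. The 95% is the expected rate of meeting the Week 12 endpoint, so it already includes anyone rescued before Week 12.

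**3. Weight of one patient**

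1/76 = 1.3 percentage points. Expected control failures: 0.05 × 76 = 3.8.

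**4. Dilution, as illustration only**

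(a) Assume that 95% v 83% are rates before rescue, and that a share r of failures in each arm is rescued and scored as cured. The documents supply neither assumption. Apparent difference = 0.12 × (1 − r). Score test, margin 0.12, 76 per arm:

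| r | Apparent rates | Difference | Chance of claiming non-inferiority |
|---|---|---|---|
| 0 | 95% v 83% | 12 points | 2.2% |
| 0.25 | 96.25% v 87.25% | 9 points | 8.0% |
| 0.50 | 97.5% v 91.5% | 6 points | 26.6% |

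(b) Take the 73% Week 4 response in the OPAT cohort (Preliminary studies) and the planned 95% at Week 12. The share of control Week 4 non-responders who later meet the criteria is then (0.95 − 0.73)/(1 − 0.73) = 0.815. Suppose the oral arm is 20 points worse at Week 4, at 53%. Its Week 12 rate is 0.53 + r × 0.47:

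- r = 0.815: Week 12 deficit 3.7 points
- r = 0.7: 9.1 points
- r = 0.6: 13.8 points
- r = 0.5: 18.5 points
- r = 0.4: 23.2 points

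The gap shrinks unless the oral-arm share falls below 0.22/0.47 = 0.47, and widens below that.

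**5. Power of an analysis that counts rescue as failure**

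Same score test, 76 per arm, equal true rates: 84% at 95% cure, 65% at 90%, 53% at 85%.

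**The case against.** The strongest reply is that the trial compares treatment strategies. Both arms get the same oral extensions under the same response rule, Week 4 response (before any extension) is the main secondary endpoint, and the rescue events are pre-specified and reported. Scoring the Week 12 state whatever was added on the way is a legitimate choice. That stands: the primary endpoint need not be redefined to make rescue a failure.

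It is also fair that only one sentence, in the abstract, carries the *by* rule. A reader might infer that the body of the protocol contradicts itself as well, but the Study visits sentence gives only the failure side. All participants return at Week 12, and the drop-out imputation requires contact at about day 84, which fits an *at* reading. This narrows the conflict without removing it, because the abstract's sentence still scores the same patient the opposite way.

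A reader might set the 4.4% relapse in the Taiwan series (Background) against the planned 5% control failure and conclude that the by/at choice decides most failures. The documents do not support that. No timing is given for the 4.4%, the Hong Kong series of 112 and the OPAT cohort of 109 report no relapses, and the 95% was reasoned from mortality and selection bias.

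The point about antibiotic-free time is narrow too. Antibiotics stop once the criteria are met, so a Week 4 responder has about eight weeks off treatment at Week 12 and a Week 8 responder four. Only patients who first respond at Week 10 or 12 have less than the one month after stopping at which the OPAT cohort was read.

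**Conclusion.** The by/at conflict is real and concerns the endpoint that decides the trial. It is confined to one abstract sentence against the Objectives and Study endpoints, and is settled by wording. Its numerical effect cannot be estimated from the documents beyond the 1.3 points per reclassified patient at 76 per arm.

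It is also confirmed that drained, escalated or still-treated patients can be scored as cured under either reading. Dilution toward non-inferiority is plausible over a wide range, but its size, and in extreme cases its direction, depends on rescue rates in each arm that are not given. The 8.0% and 26.6% could be read as an inflated type I error. They are not. They treat a rate already defined on the Week 12 endpoint as a pre-rescue rate, the rescue shares are assumed, and on the protocol's own endpoint a 9- or 6-point deficit lies inside the margin. Nor do the documents support requiring a rescue-as-failure analysis to agree before non-inferiority is claimed. That would be a co-primary endpoint with no sample size, resting on treatment decisions made with allocation known.

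**What to change.** 1. Align the abstract, and the sentence in Study visits and procedures, with the Objectives and Study endpoints: cure means that all criteria are met at the Week 12 visit. State that death before Week 12 is a failure, in both the ITT and per-protocol analyses.

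2. Pre-specify one supportive sensitivity analysis of the primary comparison, reported beside the primary result and not a condition for claiming non-inferiority. In it, unplanned drainage, escalation of antibiotics, a metastatic complication, new *K. pneumoniae* bacteremia, or still being on antibiotics for the abscess at Week 12 counts as failure.

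The cost is protocol wording and one more analysis. No new data are needed: the events are already endpoints, and Table 1 records antibiotic history at every visit including Day 84. The downsides should be stated with the analysis. It has more failures and hence less power (84% falling to 65% or 53% if cure drops to 90% or 85% in both arms), and escalation and drainage are open-label decisions that may not be taken alike in the two arms.

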**Discussion:**

Our results would help inform local and international practice guidelines regarding the optimal antibiotic management of Klebsiella liver abscess. A finding of non-inferiority may translate to the wider adoption of a more cost-effective strategy that reduces hospital length of stay and improves patient-centered outcomes and satisfaction.

**Trial registration:**

Clinical trials gov NCT01723150

## Background

While *Klebsiella pneumoniae* is an emerging cause of community acquired liver abscess in Asian populations, there are no clear guidelines on appropriate management. Klebsiella liver abscess (KLA) syndrome differs from other pyogenic liver abscesses in that patients tend to have a normal biliary system and poorly controlled diabetes is a predisposing factor. The increased incidence in Asia is likely explained by the prevalence of the K1 and K2 capsular serotype in this region. These virulence factors possessed by *K. pneumoniae* are thought to protect from phagocytosis by neutrophils, and are associated with septic metastatic complications to brain and eye [1]. In Singapore, KLA has become the most common type of liver abscess [2,3]. In Taiwan, a retrospective study of 182 cases of pyogenic liver abscess included 160 cases of *K. pneumoniae* monoinfection [4]. All 160 *K. pneumoniae* isolates were resistant only to ampicillin, and sensitive to cephalosporins (typical of the community acquired *K. pneumoniae* strain). Of the *K. pneumoniae* patients, 67.5% had frank diabetes and an additional 7.5% had impaired glucose tolerance. Only 0.6% had intraductal stones, and none had intra-abdominal pathology. This contrasts sharply with the 77.3% of the polymicrobial abscess patients with intraductal stones and 18.2% with intra-abdominal malignancy. Mortality from KLA was 11.3%, and relapse was 4.4%.

Management of KLA consists of antibiotics, and in most instances drainage (surgical or radiological). Most guidelines support drainage of pyogenic liver abscesses where possible. There are a number of options; radiologic guided needle aspiration or catheter drainage, or surgical drainage. Surgical drainage is usually reserved for those that are inaccessible by the percutaneous route. Both catheter drainage and intermittent needle aspiration appear to be effective for small abscesses in two randomized controlled trials [5,6]. One randomized trial found catheter drainage to be superior for abscesses over 10 cm [7], however two thirds of the patients in this study had amoebic abscesses. There are no randomized controlled trials comparing drainage with no drainage, but observational data has shown that patients with abscesses over 5 cm that are not drained have worse outcomes [8]. Abscesses under 5 cm that were not drained did not have worse outcomes.

The intravenous (IV) phase of antibiotic management usually consists of either IV ceftriaxone or cefazolin (with or without concomitant gentamicin). A retrospective observational study of 107 patients in Taiwan in 2003 found higher rates of complications (metastatic infection and death) in the 59 patients in the cefazolin group, compared to the 48 patients treated with an extended-spectrum cephalosporin (36.7% versus 6.3% respectively) [9]. Within the cefazolin arm there were higher rates of severe outcomes in the nine patients not receiving concomitant gentamicin, but this failed to reach significance. In 2008, another retrospective series of 110 patients was reported from Taiwan wherein 95% of the patients received cefazolin plus gentamicin [10]. The reported low rates of metastatic complications of 4.3% and mortality of 5.4% in those treated with cefazolin plus gentamicin appear at odds with the high rates seen in the cefazolin arm of previous study. A randomized controlled trial is due to be completed soon in Taiwan, comparing moxifloxacin 400 mg IV daily for 14 days, then 400 mg *per orale* (po) daily for 7 days, with ceftriaxone 2 g IV 12 hourly for 14 days, then oral cephalexin 1 g six hourly for 7 days. The study includes all pyogenic liver abscesses (although in Taiwan the majority will be *K. pneumoniae*) [11]. This is a pilot study, aiming to enroll 48 patients by April 2012. Whilst both arms complete the same duration of IV antibiotics, moxifloxacin has a bioavailability of 90%, so if both drugs are shown to be equivalent, this study may add support to earlier conversion to orals.

Currently, there is considerable variation in practice with regard to total antibiotic duration and more specifically the duration of IV antibiotics. There is a lack of evidence to guide practice in this area which our study aims to definitively address. A retrospective study by Ng in Hong Kong in 2002 identified 112 patients with pyogenic liver abscess (most commonly *K. pneumoniae*) and grouped them into two groups based upon their management [12]. Group 1 was those that received IV antibiotics for their whole treatment course, and group 2 were stepped down to oral antibiotics once clinically stable. Group 1 received on average 5.9 weeks of IV antibiotics. Group 2 received three point two weeks of IV and two point nine weeks of oral. There were three deaths in the group receiving continuous IV therapy, and none in the early step-down group. No statistically significant difference in outcomes was found, and no patients relapsed. The retrospective nature of this study limits the interpretation, because allocation to the two groups was not random so there is likely to be significant selection bias. While the study was not powered to show non-inferiority, there is no suggestion of a trend towards worse outcomes in those receiving shorter courses of IV antibiotics. This adds support to the need for prospective randomized studies looking at shorter durations of IV antibiotics for KLA.

There is one randomized controlled trial that has attempted to address the question of when to convert to oral antibiotics, conducted in Taiwan [13]. Any liver abscess was eligible, but the vast majority were *K. pneumoniae* monoinfection. The study was an open label randomized controlled trial, designed as a pilot study. The study arm was oral fleroxacin (a fluoroquinolone) for three weeks, starting from the day of enrollment (patients who had already been on antibiotics for 48 hours were excluded). The control arm was IV cefazolin 1 g eight hourly plus gentamicin 1 mg/kg eight hourly for two weeks, followed by oral cephalexin 1 g six hourly one to two weeks. Exclusion criteria were: pregnancy, breastfeeding, allergy to study drugs, glomerular filtration rate (GFR) < 30 ml/min, neutrophils < 0.5×10^3^/μl, prior treatment with effective antibiotic within 48 hours of enrollment, organisms resistant to study drugs. Sixty-one patients were enrolled. After exclusions 44 were followed-up. The endpoints were bacteriologic cure (70% in the oral arm versus 81.8% in the IV arm), clinical cure two weeks post completion (60% in the oral arm versus 81.8% in the IV arm). There was one death in each arm. This study has a number of limitations. Neither endpoint was adequately defined in the study. The study was not powered for non-inferiority. Patients in the control arm were reviewed on the ward every day, whilst patients in study arm were discharged home with less frequent medical input. The control arm received cefazolin, which is possibly not the most efficacious comparator [9]. Despite the limitations, this study highlights the need for a well designed randomized-controlled trial powered to show non-inferiority.

Currently, no local guidelines exist and there is wide variation in clinical practice. Based only upon the limited studies mentioned above, a number of organizations have written recommendations for the management of pyogenic liver abscess. These do not specifically address KLA and give variable advice to clinicians regarding the optimal time to step-down to oral therapy. The Australian Therapeutic Guidelines recommend 'After clinical improvement, consider a step-down to oral therapy. The total treatment duration should be four to six weeks’ [14]. The BMJ Best Practice Guidelines recommend that 'Parenteral therapy is given initially. If the patient is improving and fever and leukocytosis have resolved, the patient can be switched to an oral anti-infective regimen, typically for four to six weeks’ [15]. UpToDate recommends a total of four to six weeks, with IV antibiotics for the first two to three weeks if drained, or four to six weeks if not drained [16]. The results of our study will provide an evidence base for local and international guidelines.

